##### School Nurses

The LCSD includes 21 schools serving 11,500 students. Each of these schools has at least one dedicated nurse: a licensed practical nurse or a registered nurse. Once patient participants are identified, I will contact the nurses at the school they attend to review the study and obtain their consent to participate. Once the participants have been enrolled, they will participate in targeted training, as described in the following sections.

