#### Training

##### Primary Care Provider and School Nurses

I will conduct one-on-one sessions with the PCP and school nurses to explain how the patient enters information (ie, medication administration and symptoms) into the app. For the school nurses, I will demonstrate how to access the digitally encrypted information using their site-based computers, which are available at all LCSD schools, as well as provide a short manual of instructions that will include screenshots and frequently asked questions.

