##### Quantitative Data Collection

We will perform medication counts monthly; asthma medications that do not have counters or individual vials, such as some metered-dose inhalers, will be fitted with a PuffMinder, a digital inhaler dose counter. These results will be compared to the self-report medication adherence information entered into the app by the parent or caregiver.

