### Potential Limitations and Solutions

The results from Aims 1 and 2 will be used to refine the intervention for Aim 3. For example, if we find that the PCP prefers to communicate with the school nurses via secure email instead of by phone, we will adjust the procedures. If the school nurses have issues accessing the data, I can offer additional training. As self-reports of adherence may be inflated, we will compare medication counts with information entered into the app by the parent or caregiver. Finally, even though AMD-Sp is easy to use and will require approximately five minutes of the parent’s or caregiver’s time to log symptoms and medication adherence information, if the parent or caregiver is having difficulty using the technology, my bilingual research assistant will provide additional support. I will be tracking app usage for the first week of each new enrollee to discuss concerns and strategies. We are aware of the possibility that these participants may have some unknown difficulties. If this preliminary step reveals this to be an issue, we can consider simple modifications to the study plan, such as the use of a short messaging service (ie, text messaging, which is associated with improved chronic disease management) in lieu of the app.

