#### Data Collection

Anticipated quantitative data that will result from Aim 3 include the information entered into the app by the parent or caregiver, which are then encrypted and transmitted to the school nurse. These data will include selected NIH and Agency for Healthcare Research and Quality standardized asthma outcomes [30], including the primary outcome measures of medication adherence information (ie, asthma medication ratio [31], which is predictive of childhood asthma ED visits and hospitalizations) and school days missed. This school district requires HIPAA waivers to allow communication between school nurses and local health care providers and will be able to provide information on recorded school absences once informed consent forms are obtained. Secondary outcome measures include frequency of rescue inhaler use, as well as asthma exacerbations, outpatient clinic visits, and ED visits (see Table 2). Lung capacity will be obtained using spirometry pre- and postintervention [32] to obtain relevant lung function variables, such as FEV1 (forced expiratory volume in 1 second) and FEV1/FVC (forced vital capacity). Measures from the control group will include medication counts, number of asthma exacerbations, ED and outpatient clinic visits, and spirometry measures on enrollment, during the intervention phase, and again at the end of the intervention.

**Table 2 table2:** Outcome measures and their details.

Outcome variable	Description	Source of data	Type of measure
Medication adherence—asthma medication ratio (primary outcome)	Medication administration data uploaded to the app	Parents	Continuous
Medication adherence—asthma medication ratio (primary outcome)	Medication counts performed monthly by the principal investigator	Principal investigator	Continuous
School days missed	School absences secondary to asthma symptoms	Nurses	Continuous
Asthma exacerbations	Number of asthma exacerbations uploaded to the app	Parents	Continuous
Frequency of rescue inhaler use	Albuterol usage for wheezing episodes	Parents	Continuous
Emergency department visits	Number and dates of emergency department visits uploaded to the app	Parents	Categorical
Outpatient clinic visits	Number and dates of outpatient clinic visits uploaded to the app	Parents	Continuous

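### Table 2 takes rescue inhaler use from parents alone, with no stated route for albuterol given at school and no stated control-group data for this outcome

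*Protocol article*

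**What the plan says.** In the protocol article, Aim 3, Data Collection, the outcome is secondary: "Secondary outcome measures include frequency of rescue inhaler use". Table 2 describes it as "Albuterol usage for wheezing episodes", gives parents as the source and types it as continuous. Table 2 assigns sources outcome by outcome. Nurses are the source for absences, and the principal investigator is the second source for the asthma medication ratio.

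The described data flow starts with the family. Aim 3 data include "information entered into the app by the parent or caregiver, which are then encrypted and transmitted to the school nurse". In the Aim 2 training section, which Aim 3 adopts, the article says of the nurses: "I will demonstrate how to access the digitally encrypted information using their site-based computers". Entry of doses by nurses is not described.

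The School Nurses section says of the district's schools: "Each of these schools has at least one dedicated nurse: a licensed practical nurse or a registered nurse". Nurses at the participants' schools are asked for consent and take part in the study.

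There is a second stream of medication data. Table 2 lists "Medication counts performed monthly by the principal investigator", under the asthma medication ratio. Aim 2, Quantitative Data Collection, adds that "asthma medications that do not have counters or individual vials, such as some metered-dose inhalers, will be fitted with a PuffMinder". Neither place mentions inhalers kept at school.

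The Data Collection section closes with the control-group measures: medication counts, exacerbations, emergency and outpatient visits, and spirometry. Frequency of rescue inhaler use is not among them.

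**The concern.** During the school day a parent does not see the child use a rescue inhaler. Where the parent is the only named source, a school dose reaches the record only if someone tells the parent and the parent then logs it. That invites undercounting in both arms.

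Undercounting by the same proportion in both arms lowers the level but leaves the between-group ratio alone. The harder problem is that the intervention is meant to improve communication between parents and school nurses. Whether a parent hears of a school dose may then depend on the assigned arm, so the completeness of the outcome could itself be affected by treatment.

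The Power Analysis section says that the study's purpose is to obtain effect size estimates for later work. An estimate for rescue use that mixes a change in use with a change in recording would be a poor basis for planning. Without stated control data, the comparison has no defined second side.

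**Working it through.** **Figures in the plan.** The article gives no figure for rescue use or for its split between home and school. Its only statistical figures are the power statements for the asthma medication ratio. These reproduce with a one-sided two-sample t-test at .05 and 10 per group: power is 0.530 at an effect size of 0.80 (stated .53), and the effect detectable at 80% power is 1.156 (stated 1.16). They do not bear on this point.

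**Step 1: can a school dose enter the record for this outcome?**
- Nurse entry: none is described. The app carries parent input to the nurse, and nurses are trained to read it.
- Nurse as source: Table 2 names nurses for absences only.
- Monthly counts: assigned to the asthma medication ratio, with school-kept inhalers not mentioned.
- Parent entry at second hand: possible, but no step is described for telling the parent of a school dose.

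So there is no stated route. That is weaker than saying that such doses cannot be recorded.

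**Step 2: what would incomplete capture do?** Let *s* be the share of rescue doses taken at school and *c* the share of those that parents log, with subscripts I (intervention) and C (control). If true total use is equal in the two arms, then

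apparent ratio = [1 − s_I(1 − c_I)] / [1 − s_C(1 − c_C)].

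All values of *s* and *c* below are assumptions. The value of one third for *s* comes from assuming 7 of 15 waking hours at school on 5 of 7 days: (7 × 5)/(15 × 7) = 0.33. This is a share of waking hours, and the share of doses may be quite different.

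With *s* equal in both arms:

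| s | c equal in both arms | c_I = 0.5, c_C = 0 | c_I = 0, c_C = 0.5 |
|---|---|---|---|
| 10% | 1.00 | 0.95/0.90 = 1.06 | 0.90/0.95 = 0.95 |
| 20% | 1.00 | 0.90/0.80 = 1.125 | 0.80/0.90 = 0.89 |
| one third | 1.00 | 0.833/0.667 = 1.25 | 0.667/0.833 = 0.80 |

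In the first column the ratio is unbiased, but the level is still too low by *s*(1 − *c*): with no capture, by 10%, 20% or 33%. In the other two columns the bias goes either way. Better communication in the intervention arm (the middle case) would make the intervention look worse.

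**Step 3: are there control data?** Set side by side, Table 2 lists rescue use as an outcome without splitting it by arm, and the control-group list leaves it out. The article also does not say whether waiting-list families use the app while they wait. The source of control-group rescue data is therefore not stated.

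**The case against.** The strongest reply is that the source column says who enters the data, not which doses count. Nothing stops a parent logging a dose that the nurse has reported, and the app exists to ease day-to-day contact between the two. Figure 2, the protocol diagram, was not available for this check, and Aim 3 will use a refined protocol. This stands against any claim that school doses are not recorded. It does not supply a route: the contact described runs from parent to nurse, and Table 2 is the stated choice of source.

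A second reply is that objective data exist. Monthly counts are planned, counters are fitted to inhalers that lack them, and of self-reports, which may be inflated, the article says "we will compare medication counts with information entered into the app by the parent or caregiver". Medication counts are also listed for the control group. This stands in part. A counter registers a dose whoever sees it, so the counts could fill much of the gap if they covered albuterol and any inhaler kept at school. The article does not say that they do, and it ties the counts to another outcome.

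Third, the control-group list may not be exhaustive, since it also omits school days missed, a primary outcome. That is fair, and is why the point is that control data for rescue use are unstated rather than ruled out.

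A reader might also infer that a nurse-based intervention moves rescue doses into school hours, so that they vanish from the parents' record and the intervention looks better. The arithmetic is easy: with 10% of doses at school in control, 30% in intervention and none logged, the ratio is 0.70/0.90 = 0.78. But nothing in the article says that the intervention has nurses give albuterol or shifts doses to school. The described role is communication and access to app data. That direction is a hypothesis.

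**Conclusion.** The point holds in a limited form. Table 2 names parents as the sole source for rescue inhaler use in schoolchildren, no route for school-given albuterol is described, and the control-group list omits the outcome. Following the plan as written can undercount school doses, and the degree may differ by arm because the intervention targets parent-nurse communication.

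The documents do not support going further on size or direction. Under the assumed shares in the table, with equal true use, the apparent ratio runs from 0.80 to 1.25, and it is 1.00 whenever school share and capture are equal in the two arms. These are illustrations, not estimates.

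Nor should the problem be carried over to the asthma medication ratio as established. The article does not give the ratio's formula, and the ratio has the monthly counts as a second source. If rescue doses enter its app-based version, that version would share the gap.

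The weight is modest: one secondary outcome in a feasibility trial of 20 families. The correction is nonetheless specific and inexpensive.

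**What to change.** - In Table 2, set the source of rescue inhaler use to parents plus the school nurse's record of albuterol given at school.
- State that the monthly medication count includes any inhaler kept at school.
- Collect both in the same way in both groups from randomisation, and add rescue use to the control-group measures in Aim 3, Data Collection.

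The cost is one table row, one addition to the control-group list, and a school record request for 20 children to nurses who already take part in the study. The article mentions district records only for absences and mentions no school medication record, so the consent form and HIPAA release would need wording that covers this request. The change concerns data sources only and touches no clinical rule.

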#### Data Security

Biometric data are shared by the parent with the school nurse and PI through the AMD-Sp app by selecting and sending all uploaded information directly to the designated recipients. The app will be password protected to prevent unauthorized access to the information in case of phone loss [33].

#### Power Analysis

Formal power analyses are not presented for this study, because (1) we do not have useful effect size estimates and (2) the resources available for K23 research virtually insure an underpowered research design. Our sample of 20 (10 in each group) thus represents far less than .80 power. We will have power to detect an effect size of 1.16 in the mean asthma medication ratio between the intervention group and control group; the power to detect a large effect size (0.80) is .53 [34,35]. Our goals are to arrive at effect size estimates for future work.

#### Statistical Analysis

The main analysis for Aim 3 will be to compare the average adherence between the case and control groups. This comparison will be made via PROC REG in SAS, version 9.4 (SAS Institute) [36]. We will also compare mean rates of the asthma medication ratio using the Wilcoxon rank-sum test. A 1-sided *P* value of .05 will be considered significant for all analyses. I anticipate that the results will support the rationale for an RCT focused on a scalable, multisite, multicounty version of this intervention, with state-level stakeholders such as Select Health, at the conclusion of this study.

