### Theoretical Framework

My preliminary studies and proposed study are guided by a bio-ecological conceptualization of the complex interactions and intersections of multilevel factors with childhood asthma management in a specific vulnerable population group: rural Latino children with asthma. I will use Bronfenbrenner’s Process-Person-Context-Time model to organize the study approach, intervention design, and data analysis (see Table 1) [20]. The concepts in this model allow for identification and examination of relevant variables that contribute to poorer health care outcomes (eg, communication issues within and between patients and system representatives, where people live, health care accessibility, socioeconomic status, demographics, individual knowledge, and how people and environments change over time).

**Table 1 table1:** Bronfenbrenner’s Process-Person-Context-Time model and ecological levels.

Ecological level	Associated factors
Microsystem	Patient: knowledge deficits and medication adherence School nurse: knowledge and informational deficits Primary care provider: knowledge and informational deficits
Mesosystem	Interactions between the patient and family and school nurses Interactions between the patient and family and provider Interactions between the provider and school nurses
Exosystem	Effects of transportation issues Effects of work attendance constraints Effects of documentation status
Chronosystem	Knowledge change over time Medication adherence over time Biophysical measures over time Emergency department visits (retrospective and prospective) Sustainability of program after feasibility study is complete

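### The main adherence comparison names no baseline term; prespecifying one, measured alike in both arms, would probably sharpen the effect-size estimate from 10 families per arm

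*Protocol article*

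**What the plan says.** Under Aim 3, Statistical Analysis, the protocol article states: "The main analysis for Aim 3 will be to compare the average adherence between the case and control groups". It continues: "This comparison will be made via PROC REG in SAS, version 9.4", and then "We will also compare mean rates of the asthma medication ratio using the Wilcoxon rank-sum test". The significance rule is "A 1-sided *P* value of .05 will be considered significant for all analyses". No model terms are listed, and neither a baseline value nor any other covariate is mentioned.

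Under Power Analysis it states "Our sample of 20 (10 in each group) thus represents far less than .80 power" and "We will have power to detect an effect size of 1.16 in the mean asthma medication ratio between the intervention group and control group", gives power of .53 for an effect of 0.80, and says that the aim is to obtain effect-size estimates for later work.

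On pre-intervention data, Data Collection says "Lung capacity will be obtained using spirometry pre- and postintervention", without limiting this to one arm. Medication counts, exacerbations, visits and spirometry with an enrolment measurement are listed in a sentence about the control group. Table 2 gives the adherence sources as app entries and monthly counts. A pre-intervention asthma medication ratio is not stated for either arm.

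**The concern.** In a 20-family trial, a child's adherence before randomisation may be the best single predictor of adherence six months later. If it predicts well, leaving it out of the model leaves explainable variation in the error term. It also lets a chance difference between the arms at enrolment pass, in part, into the estimated effect. What is at stake is precision. The trial is meant to supply an effect size for a larger multisite study, and a noisier estimate is a weaker basis for planning it. PROC REG is already the chosen procedure and accepts a covariate directly, so the model change itself is small. The article places the trial in the future, so the change could be made before data exist.

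**Working it through.** **Inputs from the protocol article.** n = 10 per arm (Power Analysis); one-sided alpha .05 (Statistical Analysis); standardised effects 0.80 and 1.16 (Power Analysis). **Assumption.** rho, the correlation between baseline and 6-month adherence, is not in the document and is varied. Outcomes are taken as normal with SD 1.

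**Step 1: reproduce the plan's figures without a covariate.**
- SE of the difference = sqrt(2/10) = 0.447 SD.
- Noncentrality at 0.80 = 0.80/0.447 = 1.789; 18 df; one-sided critical t = 1.734.
- Power from the noncentral t = .530 (stated .53).
- Effect detectable with 80% power = 1.156; power at 1.16 = .802. The article prints no power level beside 1.16, but 80% fits.
- Alternatives tried do not match: the one-sided normal approximation gives .557 at 0.80; the two-sided t test gives .395, with a detectable effect of 1.325.

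Both printed figures are therefore those of an unadjusted one-sided t test.

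**Step 2: chance difference at baseline.** The baseline difference between two arms of 10 also has an SD of sqrt(2/10) = 0.447 baseline SDs. The probability that it exceeds 0.5 SD in either direction is 2 × [1 − Φ(0.5/0.447)] = 26%. Only a fraction rho of such a difference is expected to carry over to the outcome.

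**Step 3: add one baseline covariate.** The residual variance is multiplied by (1 − rho²). Estimating the slope inflates the variance on average by 1 + 1/(2n − 4) = 1 + 1/16 = 1.0625. The degrees of freedom fall to 17 (critical t = 1.740). Hence SE = sqrt[0.2 × (1 − rho²) × 1.0625].

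| rho (assumed) | SE, in SD | Power at 0.80 | Effect for 80% power |
|---|---|---|---|
| no covariate | 0.447 | .53 | 1.16 |
| 0 | 0.461 | .51 | 1.20 |
| .3 | 0.440 | .54 | 1.14 |
| .5 | 0.399 | .61 | 1.04 |
| .6 | 0.369 | .67 | 0.96 |
| .7 | 0.329 | .75 | 0.85 |

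Simulation with 40,000 trials per value agrees: .510, .540, .611 and .755 at rho 0, .3, .5 and .7.

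**Step 4: break-even.** The variance is unchanged when (1 − rho²) × 1.0625 = 1, that is rho² = 1/17 and rho = .24. Allowing for the lost degree of freedom, power breaks even at about .25. Below that, adjustment costs power, at worst .53 − .51 = .02.

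**The case against.** The strongest reply is that the article never calls the comparison unadjusted. PROC REG can hold covariates, and a condensed article may leave the covariate list to a fuller document. That is fair as far as it goes. However, the text does define the main comparison as one of group averages, the Wilcoxon test takes no covariate, and the power figures match a test without one. The stated method and its planning figures agree, so proposing a better-specified model is reasonable. Claiming that the investigator decided against adjustment is not.

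Four stronger readings are tempting, and the article does not support them:

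- **That baseline values of the primary outcome are already collected in both arms.** Enrolment medication counts are listed only for controls, and the enrolment timing in that sentence may attach to spirometry alone. A single count is also not a medication ratio, which needs a period of use.
- **That chance imbalance invalidates the planned test.** Families are randomised, so the unadjusted test keeps its type I error, and its standard error already reflects such imbalance.
- **That adjustment would remove imbalance altogether.** It removes only the part of the outcome that the measured baseline predicts. Adherence taken from earlier records, a different source from the monthly counts, might predict less well.
- **That every outcome should be handled this way.** Retrospective ED visits appear only in the theoretical framework table ("Emergency department visits (retrospective and prospective"), while Table 2 has parents uploading visits to the app. Pre-enrolment absences are not stated as collected. Linear adjustment of sparse visits in 20 children is not clearly better, and no such change is proposed for ED visits or absences.

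It also stands that the trial is a feasibility study which openly admits low power.

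**Conclusion.** The point holds as one about efficiency. The planned comparison is valid, but it names no baseline term and its planning figures assume none, so it is likely to be less precise than it could be for the stated purpose. The size depends wholly on the assumed correlation. At .5 to .7, the SE falls from 0.447 to between 0.40 and 0.33 SD, and power at 0.80 rises from .53 to between .61 and .75. At .3 the gain is negligible, and at 0 about .02 of power is lost. These figures also assume a normal outcome, 10 analysed families per arm, and a baseline value that is comparable between arms. The article does not yet secure the last of these for adherence.

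**What to change.** In Statistical Analysis, prespecify the main model as PROC REG of the 6-month asthma medication ratio on treatment group and baseline adherence, and report the adjusted difference with its confidence interval.

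In Data Collection, state how baseline adherence is obtained identically in both arms. Either extend to the intervention arm the enrolment medication counts now listed for controls, or abstract a pre-enrolment ratio for every child under the medical records releases already sought. The second route is needed if enrolment counts cover no period of use.

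For lung function, analyse post-intervention FEV1 adjusted for pre-intervention FEV1.

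The cost is one degree of freedom, at most about .02 of power if the baseline proves uninformative, and minor record abstraction.
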